### Data monitoring and communication with persons

A web-portal has been designed. The aim of the Phys-Can web portal is to facilitate collection of outcome measures in the multiple study sites and to enable easily accessible electronic self-monitoring of exercise behaviour. The participants sign on to the web portal and complete forms related to outcome assessments and self-monitoring of endurance training included as part of the intervention (those who have no access to internet fill out paper forms). The data base is located at Uppsala University and constructed according to security principles from the Division of Security at Uppsala University. All communication with the data base is encrypted and backups are performed on a regular basis in order to secure data. The web portal automatically sends e-mails or text messages to participants when the scheduled assessment is available, informing them to long on to the portal to complete the questionnaires. Participants also receive reminders by e-mail or text messages. Those who choose to complete paper forms receive the questionnaires and reminders by regular mail. The web portal also notifies research assistants by e-mail when an assessment point is about to open for a specific participant and alerts the research assistants if questionnaires are not completed within a set time frame. This enables precise monitoring of time points for both participants who use the web portal or choose to fill out paper forms. At assessment points when blood samples, fitness tests and recordings of physical activity are included, a research assistant contacts participants by phone to schedule an appointment.

### Enrolment and outcomes (Fig. 2)

**Fig. 2 Fig2:**
[figure not shown]
Enrolment and outcome measurements in Phys-Can intervention trial.^*a*^Midway through exercise intervention (3 months), ^*b*^ Directly after end of primary Oncological Treatment (OT), only participants receiving radiation therapy or chemotherapy, ^c^ Directly after end of Exercise Intervention (EI), ^d^ After end of EI, ^e^ Self-reported data on physical activity, sleep onset/end, and health economics are collected via diary during one week concurrently as wearing the Sensewear Armband. At T1, only sleep onset/end and health economics are recorded, ^f^ In participants receiving chemotherapy or radiation therapy, these variables are collected at a regular basis in clinical praxis. *MFI subscale physical fatigue

#### Primary outcome measures

Two Patient reported outcome measures (PROMs) are used to assess CRF: The MFI [41] and the Functional Assessment of Cancer Therapy: Fatigue, FACT-F [42]. The MFI is a 20-item PROM and covers the following dimensions: General Fatigue, Physical Fatigue, Mental Fatigue, Reduced Motivation and Reduced Activity.

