**Methods/design:**

Six hundred newly diagnosed persons with breast, colorectal or prostate cancer undergoing adjuvant therapy will be randomized in a 2 × 2 factorial design to following conditions; A) individually tailored low-to-moderate intensity exercise with or without behaviour change techniques or B) individually tailored high intensity exercise with or without behaviour change techniques. The training consists of both resistance and endurance exercise sessions under the guidance of trained coaches. The primary outcomes, fatigue and health related quality of life, are measured by self-reports. Secondary outcomes include fitness, mood disturbance, adherence to the cancer treatment, adverse effects, return to activities of daily living after completed treatment, return to work as well as inflammatory markers, cytokines and gene expression.

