More specific, our objectives are to:Investigate the effects of low-to-moderate intensity exercise compared to high intensity exercise on person-reported outcomes (CRF as primary endpoint), chemotherapy/radiation completion rates, medical (oncology) adverse effects, physical activity and daily function, during adjuvant/curative treatment and at long-term-follow up. In addition, intervention effects on treatment tolerability and time to recurrence of cancer will be investigatedInvestigate if supplemental BCTs increase adherence to and the efficacy of a physical exercise intervention during and after adjuvant therapy.Explore the regulation of systematic inflammatory markers and muscular expression of cytokines in response to physical training and following training to investigate whether these serve as mediators for the effects on physical exercise on CRF and HRQoL.Evaluate the cost-effectiveness of physical exercise interventions for CRF from a societal perspective.

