### Sample size

The calculated sample size was based on detecting the main factorial effects of each factor on Multidimensional Fatigue Inventory (MFI) Physical Fatigue (PF) after completed intervention [32–34]. The target main effect size was determined to be 2, which according to Purcell et al. [35] is the minimal clinically important difference for the MFI-PF. We assumed that the standard deviation (SD) of PF was 5 in all four treatment arms, which is the SD reported in Purcell et al. [35], Hagelin et al. [36] and in an ongoing study within our research group (manuscript in preparation). Because three tests (two main and one interaction effect) were planned, the 5% significance level was adjusted using Bonferroni correction. In order to have 80% power to detect a main factorial effect of 2 under the null hypothesis of no effect, 67 individuals in each of the four treatment arms are needed, with a total sample size of 268 individuals.

Further adjustments of the sample size were necessary for several reasons. First, the sample size calculation was based on the assumption of no interaction effects. However, Montgomery et al. [29] argue that, if anticipating quantitative interactions, the trial should be powered to detect those effects. Interaction effects often are much smaller in size compared to the main effects. In clinical trials, it is therefore rare to have 80% power to detect the interaction effect. For instance, given the calculated sample size in the present study, the trial would have a power of only 22% to detect an interaction effect of 1. However, in the present study a possible interaction between the factors is of clinical interest. Thus, the original sample size was doubled, increasing the power to detect the interaction between to approximately 50%. Second, to account for missing data and drop-outs, the original sample size was increased further by 30%. Third, given that we include a baseline assessment, and assuming a moderate correlation (0.3) between the MFI-PF at baseline and follow-up assessments, the sample size can be reduced by approximately 10% [37]. Combining the above, we concluded that including approximately 150 individuals in each treatment arm, 600 individuals in total, should meet the statistical requirements of the trial.

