#### Secondary outcome measures

The EORTC QLQ-30 [43] and diagnosis-specific modules (QLQ-PR25 for prostate cancer, QLQ-BR25 for breast cancer, QLQ-CR29 for colorectal cancer) are used to assess *HRQoL*.

*Mood* is assessed with Hospital Anxiety and Depressions scale HADS [44] and *Functioning in daily life* with the World Health Organization Disability Assessment Schedule WHODAS II [45].

Readiness to change physical activity behaviour (The Exercise Stage Assessment Instrument (ESAI) [46]), Exercise Barrier Self-Efficacy Scale (ESES) [47, 48], and study specific questions about outcome expectation, progressive goal attainment and perceived behavioural control are used to assess *cognitive-behavioural moderators and mediators*.

*Cardiorespiratory fitness* is measured as maximal oxygen uptake during maximal walking/running until exhaustion on a treadmill using a modified Balke-protocol [49] starting at 4 km/h with an inclination of 2%. The inclination increases with 1% each minute until reaching 12%, from which the speed increases 0.5 km/h per minute until exhaustion. Self-perceived exertion is recorded using a standardized Borg-scale [40]. Oxygen consumption and minute ventilation are measured continuously using an oxygen analyzer. Heart rate is measured using a heart rate monitor. *Maximal* upper and lower extremity *muscle strength* is assessed as one repetition maximum including chest press and seated leg press. Objectively monitored *physical activity* level, *sedentary time* and *sleep* are recorded with SenseWear Armband Mini (BodyMedia Inc., Pittsburgh, PA, USA), also found feasible and valid in cancer persons [50, 51]. The participants wear the monitor for seven consecutive days. The cut off points defining sedentary time and moderate-to-vigorous intensity physical activity are below 1.5 and above 3 metabolic equivalents (METs), respectively. The data from the monitor will be downloaded and analysed with software developed by the manufacturer (Sensewear Professional Research Software Version 8.1, BodyMedia Inc., Pittsburgh, PA, USA).

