## Discussion

The Phys-Can study aims to determine the effects of low-to-moderate and high intensity physical exercise with or without BCTs on CRF and HRQoL in persons with cancer, both during treatment and in the long-term, post-treatment survivorship period. Additionally, we will investigate the role of inflammation, cytokines and gene expression in the development and maintenance of CRF, as well as the cost-effectiveness of physical exercise programs during cancer treatment.

Systematic reviews underline the potential for physical and psychosocial benefits from rehabilitation programs including physical training [7]. Courneya et al. [10] pointed out in a recent publication the top 10 research questions related to physical training and cancer survivorship and several of them are covered in the present study, e.g. to further investigate the optimal exercise prescription (e.g. intensity), if exercise reduces the risk for cancer recurrence and influences treatment completion rates, the role of behaviour change techniques and variables that may modify/mediate the responses to exercise.

The primary outcome of the present study is CRF since that is one of the most common side effects in persons treated for cancer [7]. Based on data supporting the beneficial effects of physical exercise during oncological treatment, we will perform a large scaled, well-designed study addressing the optimal level and intensity of exercise training to prevent or reduce fatigue and improve HRQoL of persons with cancer and cancer survivors. To also identify potential biological mechanisms and underlying beneficial effects of exercise, blood samples will be analysed, and muscle biopsies obtained from a sub-sample combining an experimental pre-clinical part with an intervention implemented in the oncology clinic.

We will also perform rigorous and maximal testing of physical fitness to tailor the exercise program to the individual participant fitness level as recommended [22]. Carefully monitoring of perceived exertion, heart rate monitors and number of repetitions and loads lifted is important to control and adjust exercise intensity [26]. Furthermore, including BCTs to improve exercise adherence and maintain behavioural changes in the long-term is highlighted as important [26].

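### The primary outcome is stated inconsistently, and the three-test Bonferroni split covers one scale only, so the 5% family-wise error is not guaranteed

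*Protocol article*

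**What the plan says.** The protocol article describes the primary outcome in several places, and they do not agree.

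- **Abstract, Methods/design:** "The primary outcomes, fatigue and health related quality of life, are measured by self-reports". This is plural and covers two constructs.
- **Background, objectives:** "CRF as primary endpoint". This is fatigue alone, with no scale named.
- **Discussion:** "The primary outcome of the present study is CRF since that is one of the most common side effects". Again one construct and no scale.
- **Primary outcome measures:** "Two Patient reported outcome measures (PROMs) are used to assess CRF: The MFI [41] and the Functional Assessment of Cancer Therapy" (fatigue scale). The MFI is described as covering "General Fatigue, Physical Fatigue, Mental Fatigue, Reduced Motivation and Reduced Activity", and none of the five dimensions is marked as the primary one.
- **Secondary outcome measures:** "The EORTC QLQ-30 [43] and diagnosis-specific modules" are listed here as the measures of HRQoL, against the Abstract.
- **Sample size:** the calculation uses MFI Physical Fatigue only (effect 2, SD 5). On alpha it says: "Because three tests (two main and one interaction effect) were planned, the 5% significance level was adjusted using Bonferroni correction".
- **Statistical analysis:** the two main effects and the interaction, at completion of the intervention, are the primary parameters. No scale is named.
- **Fig. 2 legend:** a footnote reads "MFI subscale physical fatigue". The figure is not shown, so the item that carries the asterisk cannot be seen.

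No section gives an order of testing or an alpha split across scales.

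**The concern.** The alpha adjustment and the list of primary outcomes do not match. The divisor of 3 counts factorial effects on one scale. The Primary outcome measures section offers two instruments, and the Abstract adds a second construct. If more than one scale has primary status and each effect on each scale is tested at 0.05/3, there are more confirmatory tests than the adjustment covers.

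What is at stake is which result confirms the trial's hypothesis. As the text stands, a reader of the results could not show from this article that the reported primary scale was the one fixed in advance.

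**Working it through.** **1. Reproduce the plan's own figures, to see which alpha it used.**

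Inputs (Sample size section): effect 2, SD 5, power 80%, three tests, four equal arms. The article does not say whether tests are one- or two-sided; two-sided is assumed. Per-test alpha = 0.05/3 = 0.01667, z = 2.394.

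- Each main effect compares one half of the sample with the other. n per factor level = 2 × SD² × (z_alpha + z_power)² / effect² = 2 × 25 × (2.394 + 0.842)² / 4 = 130.9, so 131. That is 66 per arm, 264 in total.
- With the noncentral t distribution (df = N − 4), 66 per arm gives 79.9% power and 67 gives 80.6%. The stated 67 per arm (268 in total) is reproduced.
- Interaction of 1, on the same contrast scale as a main effect: SE = 2 × 5/√268 = 0.611; power = Φ(1/0.611 − 2.394) = 22.5% (stated 22%). At N = 536 it is 46.9% (stated about 50%).

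So the plan's figures correspond to 0.05/3 per test, two-sided, on one scale.

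**2. Family-wise error if more scales are tested at the same level.**

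With k tests the Bonferroni bound is k × 0.01667, and under independence the error is 1 − (1 − 0.01667)^k. Scales measured in the same patients are correlated. The documents give no correlation, so it is an assumption, shown as a range. The correlated figures come from a simulation of 400,000 draws, with correlation between scales within each effect and the three effects independent.

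| Scales treated as primary | Tests | Bound | Independent | r = 0.7 | r = 0.9 |
|---|---|---|---|---|---|
| MFI Physical Fatigue | 3 | 5% | 4.9% | – | – |
| plus FACT-F | 6 | 10% | 9.6% | 8.5% | 7.2% |
| plus one HRQoL scale | 9 | 15% | 14.0% | 11.4% | 8.7% |

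**3. Cost of a six-way split, if FACT-F stays co-primary.**

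Per-test alpha = 0.05/6 = 0.00833, z = 2.638. Assume 420 analysed (600 less 30%) and the plan's baseline correlation of 0.3.

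- SE = (2 × 5/√420) × √(1 − 0.3²) = 0.488 × 0.954 = 0.465.
- Main effect of 2: 2/0.465 = 4.297 before rounding; Φ(4.297 − 2.638) = 95%.
- Interaction of 1: 1/0.465 = 2.148 before rounding. Under the three-way split Φ(2.148 − 2.394) = 40%; under the six-way split Φ(2.148 − 2.638) = 31%.
- At N = 536 without baseline adjustment, interaction power goes from 46.9% to 37.3%.

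**The case against.** The best defence is that the operative sections agree with each other. The Sample size section plans three tests and bases them on MFI Physical Fatigue; the Statistical analysis section names the same three effects at the same time point. For that family Bonferroni over three is correct. The Fig. 2 footnote may mark this subscale as the primary measure, and the analysis plan, which is not shown, may set out a hierarchy. On this view the fault is loose wording in a condensed article.

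Much of this stands. A reader might infer that the 5% error rate fails outright. The documents do not support that: no sentence says that FACT-F, another MFI dimension or HRQoL will be tested at 1.67%, or that success on any one scale counts as primary success. The six- and nine-test families are readings of the text, not stated rules.

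A reader might also count all five MFI dimensions plus FACT-F as primary: 18 tests, with a bound of 30%. That goes too far. The section describes what the MFI covers and does not call every dimension an endpoint.

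The defence does not remove the contradiction. No visible sentence calls MFI Physical Fatigue the primary outcome; it has to be inferred from the sample size and from a footnote whose referent is not visible. Even if the figure does mark it, the Abstract and the Primary outcome measures section still say something else. An analysis plan can add detail, but it should not have to choose between conflicting primary outcomes in the protocol.

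**Conclusion.** The inconsistency is real and can be read directly from the article. Its consequence for the error rate is conditional: 5% is kept under one reading of the text and exceeded under others that the text also allows. The excess is moderate if FACT-F shares primary status and larger if an HRQoL scale does too. Even a between-scale correlation as high as 0.9 does not bring either case back to 5%. These sizes rest on the assumed correlation range, on two-sided tests, and on every test being run at 0.05/3.

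The point should be settled before outcome data are seen, because it decides which result is confirmatory.

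**What to change.** **Preferred.** Name MFI Physical Fatigue at completion of the intervention as the only primary outcome, in the same words throughout. Make FACT-F and the other four MFI dimensions secondary, and keep HRQoL secondary. Correct the Abstract and the Primary outcome measures section to match, and name the scale in the Statistical analysis section. This uses the scale and time point that the sample size already rests on, so the sample size, the three contrasts and alpha are unchanged. The cost is that FACT-F and HRQoL can no longer support a confirmatory claim.

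**If FACT-F is to stay co-primary.** Split alpha over six tests and state the cost. Under the assumptions of step 3, power for a main effect of 2 remains high. The loss falls on the interaction, which is the reason the plan gives for doubling the sample, and its power was already well below 80%.

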#### Secondary outcome measures

The EORTC QLQ-30 [43] and diagnosis-specific modules (QLQ-PR25 for prostate cancer, QLQ-BR25 for breast cancer, QLQ-CR29 for colorectal cancer) are used to assess *HRQoL*.

*Mood* is assessed with Hospital Anxiety and Depressions scale HADS [44] and *Functioning in daily life* with the World Health Organization Disability Assessment Schedule WHODAS II [45].

Readiness to change physical activity behaviour (The Exercise Stage Assessment Instrument (ESAI) [46]), Exercise Barrier Self-Efficacy Scale (ESES) [47, 48], and study specific questions about outcome expectation, progressive goal attainment and perceived behavioural control are used to assess *cognitive-behavioural moderators and mediators*.

*Cardiorespiratory fitness* is measured as maximal oxygen uptake during maximal walking/running until exhaustion on a treadmill using a modified Balke-protocol [49] starting at 4 km/h with an inclination of 2%. The inclination increases with 1% each minute until reaching 12%, from which the speed increases 0.5 km/h per minute until exhaustion. Self-perceived exertion is recorded using a standardized Borg-scale [40]. Oxygen consumption and minute ventilation are measured continuously using an oxygen analyzer. Heart rate is measured using a heart rate monitor. *Maximal* upper and lower extremity *muscle strength* is assessed as one repetition maximum including chest press and seated leg press. Objectively monitored *physical activity* level, *sedentary time* and *sleep* are recorded with SenseWear Armband Mini (BodyMedia Inc., Pittsburgh, PA, USA), also found feasible and valid in cancer persons [50, 51]. The participants wear the monitor for seven consecutive days. The cut off points defining sedentary time and moderate-to-vigorous intensity physical activity are below 1.5 and above 3 metabolic equivalents (METs), respectively. The data from the monitor will be downloaded and analysed with software developed by the manufacturer (Sensewear Professional Research Software Version 8.1, BodyMedia Inc., Pittsburgh, PA, USA).

*Medical and clinical background data* are collected from the records of the Regional Quality Registers and from case records covering treatment administrated, dose intensity, toxicity and adverse events according to NCI-CTC 4.0 and time to cancer recurrence and survival. The Statistics and Result database (STORE) will be used to obtain data on sick days and return to work. The STORE database is managed by the Swedish Social Insurance Agency, and contains information on social insurance for all Swedish residents.

Data from several registries are included and data on persons’ and relatives’ *costs* (time and money) *related to health care utilization* will be collected. Euroqol EQ5D [52] is used to calculate *Quality-adjusted life years* (QALYs).

*Blood samples* are drawn and analysed for the levels of IL-6, IL-8, IL-1β, TNF-α, P-CK-MB, P-CRP, IGF-1, B-HbA1C, P- Cholesterol, P-HDL and P-LDL. Frozen sera are saved in bio-banks for further analyses that can be included later. *Muscle cellular outcomes* will be evaluated on muscle biopsies obtained form *m. vastus lateralis* in a subsample of women with breast cancer. A total of 200 mg tissue will be collected at three time points; before the start of adjuvant chemotherapy, in the middle of treatment, and after the end of treatment. Muscle tissue will be divided into four pieces before further handling and freezing: 1) 20–30 mg in a nice bundle of fibres is secured for later immunohistochemically analyses (fibre area, fibre type, myonuclear number and satellite cells), 2) 50 mg designated for later homogenization and protein analyses (markers of cellular stress (HSPs and inflammatory markers), mitochondrial proteins, regulators of cell size and structural proteins), 3) 30 mg is put in RNA later for later RNA extraction and mRNA analyses, 4) 30 mg is put in RNA later for later morphological analyses on single fibres (nuclear arrangements etc.). Blood and biopsies are stored according to Swedish law in bio-banks (Uppsala IVO ref. nr. 827, Linköping IVO 519, Lund IVO 136).

### Statistical analysis

The data will be analysed according to the intention-to-treat (ITT) principle, i.e. all participants will be analyzed as randomized, regardless of whether they complete the intervention as planned. The primary parameters of interests are the three factorial effects (2 main and one interaction) after completed intervention. Each factorial effect will be estimated taking into account the stratified design following Imbens and Rubin [53]. Thus, we will provide estimates for the overall factorial effects, which are the primary parameters of interest, and also stratum-specific factorial effects which could facilitate external validity. Baseline measurements will be included in the analysis model to increase the precision of the estimates.

Drop-outs and missing values will be handled according to the following procedure. The main analysis will be based on data where missingness is handled using multiple imputations by chained equations. The specification of the multiple imputation model (e.g. choice of auxiliary variables) will be decided after comparing the subject characteristics in those with complete and incomplete data. Under the assumption of missing at random (MAR), an analysis based on multiple imputation conforms with the ITT. Due to the assumption of MAR, which could be a strong assumption to make, factorial effects will also be estimated using complete blocks only. This is a result from the permuted block design which allows for unbiased estimation of the factorial effects using the complete blocks only. Sensitivity analysis will conducted by comparing estimates from the two analyses above with estimates based on complete cases only, a pattern-mixture model, and tipping points analyses [54].

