**Fig. 1 Fig1:**
[figure not shown]
Diagram of the participant flow through enrolment, baseline measurement, randomization, and follow-up. H = high intensity training; L = low intensity training; BCT = Behaviour Change Technique

The RCT is stratified and within each stratum randomization is carried out following a permuted block design with 8 participants per block. The defined strata are the three hospitals (Linköping, Lund and Uppsala) and three cancer sites yielding 9 strata. When all baseline measurements are finalized and reported in the project’s electronic case report form, the randomization is generated automatically in a web-portal (described below) of participants to an exercise group according to predefined strata (see above). The personnel in charge of recruitment then contact the participant with information on study condition and the first visit to the gym is scheduled.

All participants will exercise at least twice weekly for a period of 6 months under the guidance of trained coaches. Training intensity is 40–50% (LM) or 80–90% (H) of each individual’s heart rate reserve (Heart rate reserve = HRpeak-HRrest) and maximal muscle strength.

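### The complete-blocks analysis is called unbiased without any missingness condition, but in general it shares the complete-case bias and does not relax MAR

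*Protocol article*

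**What the plan says.** The Statistical analysis section of the protocol article makes multiple imputation by chained equations, under MAR, the main analysis. It then adds a second analysis and gives the reason: "Due to the assumption of MAR, which could be a strong assumption to make, factorial effects will also be estimated using complete blocks only". The justification follows directly: "This is a result from the permuted block design which allows for unbiased estimation of the factorial effects using the complete blocks only". Neither sentence says what must hold about the missing data.

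These two analyses are then to be compared with "estimates based on complete cases only, a pattern-mixture model, and tipping points analyses".

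The Design section describes the blocks: "within each stratum randomization is carried out following a permuted block design with 8 participants per block". The strata are hospital by cancer site, "three cancer sites yielding 9 strata". The Sample size section gives the total, "including approximately 150 individuals in each treatment arm, 600 individuals in total", and the allowance for loss: "to account for missing data and drop-outs, the original sample size was increased further by 30"%. It gives neither an attrition rate as such nor an expected number of complete blocks.

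**The concern.** Permuted blocks balance the four arms as randomised. They do not balance the arms among blocks selected afterwards because nobody in them was lost. Nothing in the Design section makes the blocks matched sets either; they are permuted within stratum only. Discarding a whole block because one member is missing therefore removes no imbalance that the drop-out created among those who remain.

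The trial randomises exercise intensity and measures fatigue, so drop-out that depends on fatigue differently in the high and low-to-moderate arms is plausible. In that case an estimate with complete-case bias and a much larger standard error would carry the label unbiased, in the place where the plan answers its own doubt about MAR. Agreement or disagreement with the imputation result would then say little about whether MAR holds.

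**Working it through.** **Inputs.** From Sample size: total 600, target main effect 2 on MFI Physical Fatigue, SD 5, level 0.05/3, baseline correlation 0.3, a 30% increase for missing data. From Design: blocks of 8, 9 strata. Hence 600/8 = 75 blocks, with 2 participants per arm in each if balanced.

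**The plan's own figures reproduce.** A two-sided two-group t calculation (difference 2, SD 5, level 0.05/3, 80% power) needs 132.3 per factor level. Rounded up, that is 67 per arm and 268 in total, as stated. Power for an interaction of 1 is 22.5% at 268 (stated 22%) and 46.9% at 536 (stated about 50%).

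**Expectation.** Let Y be a participant's outcome and R = 1 if it is observed. A block is complete when R = 1 for all 8 members. If members drop out independently, the other seven carry no information about this participant's outcome, so

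E(Y | arm, block complete) = E(Y | arm, R = 1).

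Within a stratum, the right-hand side is the complete-case mean. Both contrasts therefore estimate the same quantity, which equals the randomised contrast only under conditions on R.

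**Numerical check.** Mechanisms below are assumed; the documents give none. SD 5 throughout; effects are high minus low-to-moderate intensity. The first two rows use 30% or 23% random loss in the low-to-moderate arms and missingness rising with fatigue in the high-intensity arms only (slope 0.8 per SD on the logit scale). The other rows have about 27% to 31% missing.

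| Mechanism | True effect | Complete cases | Complete blocks |
|---|---|---|---|
| Fatigue-dependent, high-intensity arms only, 30% loss | 0 | -1.07 | -1.07 |
| Same, 23% loss | 0 | -0.84 | -0.83 |
| Outcome-dependent in both, unequal rates | 0 | -0.42 | -0.39 |
| Outcome-dependent, identical in both | 0 | 0.00 | -0.01 |
| Outcome-dependent, identical in both | -2 | -1.74 | -1.73 |
| Baseline-dependent in one intensity group, unadjusted | 0 | -0.46 | -0.45 |
| Completely at random | 0 | 0.00 | 0.03 |

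The two estimators agree within Monte Carlo error (at most about 0.02) in every row.

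**How many blocks survive.** With independent loss d, the share complete is (1 - d)^8. The 30% allowance can be read three ways:
- As 30% attrition: d = 0.30.
- As N x 1.3: d = 1 - 1/1.3 = 0.231.
- As 30% of the original 268 added to the doubled 536: 0.3 x 268 = 80.4, and 80.4/616.4 gives d = 0.13.

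The main-effect SE with baseline adjustment is sqrt(4 x 25 x (1 - 0.3^2)/n) = sqrt(91/n).

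| d | Share complete | Blocks of 75 | People | SE, complete blocks | SE, complete cases |
|---|---|---|---|---|---|
| 0.30 | 5.8% | 4.3 | 35 | 1.62 | 0.47 |
| 0.231 | 12.2% | 9.2 | 73 | 1.11 | 0.44 |
| 0.13 | 33% | 25 | 197 | 0.68 | 0.42 |

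Against an effect of 2 at level 0.05/3 two-sided, the complete-blocks power is about 12%, 28% and 71%. With 4 to 9 complete blocks over 9 strata, some strata would very probably have none. The stratum-specific effects that the section also promises could then not be estimated from this analysis.

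**The case against.** The strongest reply is that this is a supplementary analysis. Multiple imputation is the main analysis, the sample size does not depend on complete blocks, and the pattern-mixture and tipping-point analyses already address departures from MAR. All of that stands and limits the harm. A reader might infer that the plan treats complete blocks as assumption-free or as the yardstick for the main result; it says neither.

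A reader might also infer that about 6% of blocks would survive at the planned attrition. The documents do not support that: they give an increase in sample size, not a loss rate. The plan's own total fits 30% loss worst: 536/0.7 x 0.9 = 689, against 536 x 1.3 x 0.9 = 627 and (536 + 80.4) x 0.9 = 555, with about 600 stated. The 6% is one end of an assumed range.

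Nor is the estimate biased whenever drop-out depends on arm and outcome. If retention is a product of an arm factor and an outcome factor, a true effect of 0 is estimated without bias. Equality with complete cases is exact only within strata and with independent drop-out within blocks. With unequal loss across strata, the two analyses weight strata differently. If missingness depended only on block or stratum, the complete-blocks estimate would be unbiased within strata. The simulated -1.1 illustrates an assumed mechanism and is not a forecast.

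It is also tempting to say that seven observed participants are lost for each missing one. At 30% loss, 180 are missing and 420 - 35 = 385 observed people are discarded, about 2.1 each; at 10% loss it is about 4.7.

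None of this rescues the sentence, which states unbiasedness with no condition and offers it as the response to doubt about MAR. A single counterexample is enough to refute it.

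**Conclusion.** The concern holds in a limited form. The unconditional claim of unbiasedness is incorrect. Complete-blocks estimation does not relax MAR; in general it needs stronger conditions than MAR-based imputation, such as missingness completely at random or depending only on block or stratum. Where drop-out relates to outcome differently by arm, it is generally biased in line with complete cases; an assumed but plausible mechanism gives about half the target effect. It also costs precision: on the three readings of the allowance its SE is roughly 1.6 to 3.5 times the complete-case SE (0.68/0.42 to 1.62/0.47).

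The survival figures assume independent drop-out at a uniform rate. The primary estimate and the sample size are unaffected. What needs correcting is a misstated property and the role given to this analysis.

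**What to change.** In the Statistical analysis section:

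1. Delete the sentence claiming unbiasedness, or state the conditions it needs (missingness completely at random, or depending only on block or stratum).
2. Stop presenting complete blocks as the answer to violations of MAR. Drop the analysis, or keep it as supplementary and state the expected number of complete blocks under a stated attrition rate.
3. Name the pattern-mixture and tipping-point analyses, already planned, as the check on MAR, and allow the departure from MAR to differ between the high and low-to-moderate intensity arms.

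The cost is wording and minor analysis work. Randomisation, data collection, the sample size and the main analysis stay as they are.
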